#### Cravings

The Desires for Alcohol and Drugs Questionnaire (DAQ-6) will be used to assess cravings for substances. Participants are prompted to select their drug of preference and then asked to rate their agreement towards 6- items on a seven-point Likert scale from 1- Strongly agree, to 7- Strongly disagree [28]. An example item is “I would do almost anything to have a drink/use drugs right now”. A total score is computed with higher values indicating greater cravings.

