### Follow-up

Follow-up will be conducted via telephone at 7-weeks after baseline and again at 6-months post-intervention. To ensure blind assessment of outcome measures, the primary and secondary dependent measures will be collected by an assessment officer who is naïve to allocation and study design. At the beginning of each phone call, participants will be reminded that they should not reveal their condition to the assessment officer. If participants disclose their condition, an alternative assessment officer will complete the assessment. Assessments will take approximately 30 min to complete. Multiple methods will be used to stay in contact with participants (e.g. telephone, email, SMS, social media). Alternate contact details provided by the participant will be used if there is difficulty reaching the participant. Table 1 reflects a schedule of assessments, including the primary and secondary outcomes collected at each time point.

**Table 1 Tab1:** Schedule of assessments

Domain	Data		Assessment Interval			
		Pre-Trial	Baseline	Intervention period	7-w	6-m
Recruitment	Eligibility	x ^c^				
Demographics						
	Date of Birth		x^b^			
	Age		x^b^			
	Postcode		X^b^		x^a^	x^a^
	Gender		X^b^			
	Aboriginal and/or Torres Strait Islander		x^b^			
	Marital status		x^b^			
	Sexual orientation		x^b^			
	Dependents/children		x^b^			
	Living arrangements		x^b^			
	Accommodation		x^b^			
	Education		x^b^			
	Employment		x^b^			x^a^
	Job status		x^b^			
	Previous treatment episode		x^b^			
	Mental health diagnoses		x^b^			
	Physical health conditions		x^b^			
	Medications		x^b^			x^a^
Substance use						
	TLFB (i.e. days of use)^2^		x^a^		x^a^	x^a^
	Treatment goals		x^b^		x^a^	x^a^
	Cravings (DAQ-6)^2^		x^a^		x^a^	x^a^
Loneliness						
	Single item		x^b^			
	Drinking Motivations		x^b^			
	UCLA (Version 3)^1^		x^a^		x^a^	x^a^
Social variables						
	Multiple group membership^2^		x^a^		x^a^	x^a^
	SEMSI		x^b^		x^a^	x^a^
	Use/recovery identity		x^b^		x^a^	x^a^
	Support for treatment goals		x^b^		x^a^	x^a^
Barriers to connecting						
	Self-stigma		x^b^		x^a^	x^a^
	Mini-SPIN		x^b^		x^a^	x^a^
	Young Schema Questionnaire (mistrust, emotional inhibition, defectiveness/shame)		x^b^		x^a^	x^a^
Wellbeing						
	Psychological health (K10)^2^		x^a^		x^a^	x^a^
	Suicidality (CSSRS-S)		x^a^		x ^a^	x ^a^
	Quality of life (AQoL-8D)^2^		x^a^			x^a^
Experience of Care						
	YES				x^a^	
	PREMAT				x^a^	
Service use						
	CSRI^2^		x^a^			x^a^
	Travel^2^		x^b^	x^c^	x^a^	

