### Other variables

#### Loneliness

A single item “I often feel very lonely” will be used to report prevalence of loneliness. Response options for this item are: 1 – Strongly disagree to 7 – Strongly agree. This item is taken from the Household Income and Labour Dynamics in Australia (HILDA) Survey [33] and will allow for the prevalence of loneliness to be compared to the general Australian population.

A single item from the Drinking Motivations Questionnaire (DMQ-R; [34]) will be used to determine how frequently substance use was motivated by the following reasons: “so you won’t feel left out” (item 20). This item was adapted and added to read “so you won’t feel lonely”. Response options are: 1 - Almost Never/Never to 5 - Almost always/Always.

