#### Patient experiences of care

The Patient-Reported Experience Measure for Addiction Treatment (PReMAT) [41] was designed in partnership with people accessing residential AOD treatment services and comprises 33 items that reflect aspects of care most important to people attending these services. An example item is “My day is structured here”. Each item is responded to on a 5-point Likert scale from 1 - strongly disagree to 5 - strongly agree, with total scores ranging from 31 to 155. Higher scores indicate greater levels of positive experience.

To evaluate *participant experience [with Groups for Belonging and TAU]* we will use the Your Experience of Service (YES) Survey [42]. The YES Survey is Australia’s national measure of consumer experience in mental health services. This national questionnaire was developed in partnership with mental health consumers and comprises 26 items designed to gather information from consumers about their experience of care. An example item is “Staff showed respect for how you were feeling”. The 22 items related to ‘experience’ and 4 items related to ‘outcomes’ yield response options ranging from 1 - Never to 5 - Always or 1 - Poor to 5 - Excellent. Scores for two scales (Experience Scale and Outcome Scale) will be summed to provide two summary scores.

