#### Data analysis

Statistical analyses will be managed by independent statisticians. Loneliness scores will be analyzed using linear regression in a mixed modelling framework. Fixed effects will include terms for intervention, time point (7 weeks or 6 months), an interaction between intervention and time point, baseline loneliness score, and strata (community-based vs. residential), and random effects for cluster and participant will be included to account for clustering by site, and repeated measurements on participants. The estimated mean difference in loneliness scores between the arms at the primary (6 months) and secondary (7 weeks) time points will be reported, along with 95% confidence intervals, and p-values, as summary measures of the intervention effectiveness.

The analysis set for the primary outcome will be Intention to Treat, however, sensitivity analyses using the Per Protocol analysis set will also be performed. In the case of missing data, multiple imputation methods will be utilized to ensure the analysis set is Intention to Treat. Analysis of secondary outcomes at 7 weeks and 6 months will also utilize linear mixed models (if assumptions of normally distributed residuals and constant variance are met) or generalized linear mixed models otherwise. Fixed effects will include those listed above for the primary outcome variable. Effect estimates for the difference between arms, 95% confidence intervals, and p-values, will be reported for each outcome at each follow-up time point. A sub-group analysis will be performed estimating the difference in change in loneliness from baseline among those participants who reported high loneliness scores at baseline. A secondary sub-group analysis comparing the difference in loneliness scores at 7 weeks and 6 months for residential participants compared to community-based participants will also be performed.

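### The printed DAQ-6 anchors conflict with the stated direction of the craving total; if items are summed as printed, the between-arm difference would carry the wrong sign

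*Protocol article*

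**What the plan says.** The Cravings section under Secondary outcomes makes three statements about the DAQ-6:

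- Response key: six items on a "seven-point Likert scale from 1- Strongly agree, to 7- Strongly disagree".
- Example item: "I would do almost anything to have a drink/use drugs right now".
- Direction of the total: "A total score is computed with higher values indicating greater cravings".

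Table 1 (Follow-up section) lists the measure as "Cravings (DAQ-6)^2", where the superscript marks a secondary outcome, with collection at baseline, 7 weeks and 6 months. For secondary outcomes the Data analysis section says: "Effect estimates for the difference between arms, 95% confidence intervals, and p-values, will be reported for each outcome at each follow-up time point".

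On a different instrument, the Patient experiences of care section gives the PReMAT 33 items, each rated 1 to 5, "with total scores ranging from 31 to 155".

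**The concern.** A participant with intense craving would agree with the example item and so receive a 1. A participant with none would disagree and receive a 7. Under that key a high total signals little craving, which is the reverse of what the section says. The article mentions no recoding that would reconcile the two statements.

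The DAQ-6 is a named secondary outcome and its result is an arm difference, so the sign of the estimate decides whether the result reads as benefit or harm. A reversed total has the same range and the same variance as a correct one. Routine checks of range, spread or completeness would not reveal the error.

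**Working it through.** **Inputs, all from the protocol article.** Six items scored 1 to 7, with 1 for strong agreement (Cravings); an example item that expresses craving when endorsed (Cravings); higher total means more craving (Cravings). The plan gives no numerical DAQ-6 range to reproduce.

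**Step 1: total as printed, all six items worded like the example.**
- Strongest craving, all strongly agree: 6 × 1 = 6.
- Weakest craving, all strongly disagree: 6 × 7 = 42.

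The total falls as craving rises, contrary to the stated direction.

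**Step 2: how far this depends on the unseen items.** Only one item is shown. Let r of the six be worded the opposite way. Then the strongest craving totals (6 − r) × 1 + r × 7 = 6 + 6r, and the weakest totals (6 − r) × 7 + r × 1 = 42 − 6r.

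| r | Strongest craving | Weakest craving |
|---|---|---|
| 0 | 6 | 42 |
| 1 | 12 | 36 |
| 2 | 18 | 30 |
| 3 | 24 | 24 |
| 4 | 30 | 18 |
| 5 | 36 | 12 |
| 6 | 42 | 6 |

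The raw sum runs in the stated direction only if at least four of the six items are worded opposite to the one chosen as the example. At three the two ends coincide.

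**Step 3: effect on the reported difference.** Reversing each item as 8 − response gives a reversed total of 48 − raw total. The strongest craving then scores 42 and the weakest 6, as the section intends. For arm means T and C, (48 − T) − (48 − C) = −(T − C). Adjusting for the baseline total, which is reversed in the same way, does not alter this: if raw follow-up = a + b × arm + c × raw baseline, then reversed follow-up = (48 − a − 48c) − b × arm + c × reversed baseline. The arm coefficient goes from b to −b with the same standard error, so interval width and p-value are unchanged. As an illustration, a simulation that assumed craving 0.4 SD lower in the intervention arm, with all items worded like the example, gave a difference of +2.70 as printed and −2.70 after reversal. The 2.70 depends on that assumption; the change of sign does not.

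This exact equivalence belongs to the linear mixed model. The Data analysis section allows a generalized model if residual assumptions fail. With a non-identity link the size and p-value need not be exactly preserved, but the direction would still be misread.

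**Step 4: comparison within the article.** The other agree/disagree scales with stated anchors all run from disagreement (low) to agreement (high): the single loneliness item ("1 – Strongly disagree to 7 – Strongly agree"), SEMSI, the identity items, ISMI-9 and PReMAT. The DAQ-6 is the only one printed the other way round.

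**Step 5: PReMAT, separately.** 33 items scored 1 to 5 give 33 × 1 = 33 to 33 × 5 = 165. The stated range fits 31 items: 31 × 1 = 31 to 31 × 5 = 155.

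**The case against.** The strongest reply is that the Cravings section fixes the direction of the total and does not say that raw codes are summed. For K10, SEMSI, ISMI-9 and the Mini-SPIN the article does say that items are summed; for the DAQ-6 it says only that a total is computed. A statistician who builds the total to match the stated direction gets the right sign. Item recoding is also ordinary content for an analysis plan, a data dictionary or the cited instrument source, none of which is shown. Since every other agreement scale runs the opposite way, swapped anchors in print are a plausible explanation.

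Much of this stands. The absence of a recoding sentence is not in itself a fault, and a reader might infer that the craving result will be reported with the wrong sign. The documents do not support that inference: it requires both that raw codes are summed as printed and that most of the five unseen items are worded like the example.

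The reply does not remove the contradiction. The article states a response key and a direction that disagree for the one item it shows, and a reader cannot tell which is right.

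A further objection concerns the remedy. Re-anchoring the form could mix two codings if responses have already been collected. The trial was registered on 6 February 2025 and the article published on 27 August 2025, with no recruitment status given. That objection is accepted.

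**Conclusion.** The point holds as an internal contradiction in the scoring of one named secondary outcome. If the items are summed as printed and most are worded like the example, totals run from 6 (most craving) to 42 (least), and the arm difference is reported with the wrong sign at both follow-up times. Under the linear mixed model its size, interval width and p-value are unaffected. The loneliness outcome, the sample size and the power calculation are untouched. While item responses are stored with their labels, the error can be corrected without loss of data.

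The PReMAT mismatch is certain arithmetic but minor. It involves no question of sign, and the measure is listed under Other variables and is not marked as a secondary outcome in Table 1. It adds nothing to the weight of the DAQ-6 point. It could also be inferred that two items are unscored, but the article does not say so.

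**What to change.** 1. Check the REDCap data dictionary for the DAQ-6 anchors and item wording as administered. Do not change the anchors for data already collected.
2. If the form runs from disagreement (1) to agreement (7), correct the printed anchors. If it runs as printed, state that craving-worded items are reverse-scored as 8 minus response, giving a total of 6 to 42 on which higher means more craving. If any item is worded the other way, say which items are reversed.
3. As a separate editorial correction, state which PReMAT items enter its total: 33 items give 33 to 165, and 31 items give 31 to 155.

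The cost is one sentence for each instrument and one data-dictionary check. Neither the design nor the statistical model changes.

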#### Psychological distress

The Kessler Psychological Distress Scale (K10; [30]) will be used to assess psychological distress. An example item is “In the past 4 weeks, about how often did you feel hopeless”. Each item is rated on a five-point Likert scale ranging from 1 - None of the time, to 5 - All of the time. Responses are summed to yield a score of between 10 and 50, with higher scores signaling greater levels of distress.

#### Quality of life years adjusted (economic analysis)

The Assessment of Quality of Life (AQoL-8D) [31] will be used to assess health related quality of life. This instrument will determine the cost-effectiveness of the Groups for Belonging intervention. The AQol-8D consists of 35-items and has two overarching domains, including physical and psychosocial quality of life. An example item is “How well do you communicate with others”. Higher scores on these domains indicate higher health related Quality of Life.

#### Service use (economic analysis)

A Client Service Receipt inventory (CSRI; [32]) will be used to ascertain the types and amount of service use participants have engaged in at baseline and at the 6-month timepoint. The CSRI includes items about AOD service use, health services and hospital service use, contact with the criminal justice system, and mode of travel to these services.

### Other variables

#### Loneliness

A single item “I often feel very lonely” will be used to report prevalence of loneliness. Response options for this item are: 1 – Strongly disagree to 7 – Strongly agree. This item is taken from the Household Income and Labour Dynamics in Australia (HILDA) Survey [33] and will allow for the prevalence of loneliness to be compared to the general Australian population.

A single item from the Drinking Motivations Questionnaire (DMQ-R; [34]) will be used to determine how frequently substance use was motivated by the following reasons: “so you won’t feel left out” (item 20). This item was adapted and added to read “so you won’t feel lonely”. Response options are: 1 - Almost Never/Never to 5 - Almost always/Always.

#### Treatment goals

A single item will be used to determine treatment goals: “Thinking about your primary substance(s) of concern, which of the following items best fits your goals?” Responses include: Total abstinence, never use again; Total abstinence but realize a slip is possible; Occasional use when urges strongly felt; Temporary abstinence; Controlled use; No goal.

#### Self-efficacy in managing identities

The Self-efficacy in Managing Social Identities Scale (SEMSI; [35]) will be used to examine participants’ self-efficacy in managing their identities. The SEMSI is 5-items, with response options rated on a 5-point Likert scale ranging from 1 – Strongly disagree, to 5 – Strongly agree. An example of an item on the SEMSI is “I am confident that I can make meaningful connections with members of the groups that I belong to”. Items are summed together for an overall score, with higher values indicating greater self-efficacy.

#### Suicidality

The Columbia Suicide Severity Risk Scale - Screener (CSSRS-S; [36]) will be used to assess suicidal ideation. Suicidal ideation severity is rated on a five-point ordinal scale with 1 - yes, or 0 - no responses. Points on this scale tap into the following themes: 1 - wish to be dead, 2 - non-specific active suicidal thoughts, 3 - suicidal thoughts with methods, 4 - suicidal intent, and 5 - suicidal intent with plan. A score of 3 or greater on the CSSRS–S indicates potential risk of suicide at any assessment time point.

#### Support for treatment goals

A single item was adapted from the Assessment of Recovery Capital [37] to ascertain whether participants have support to pursue their treatment goals. This item reads: “I have a network of people I can rely on to support my treatment goals”. Response options for this item are: 1 - Yes or 2 - No.

#### User/recovery identity

Three items will be used to determine participants identity in relation to their substance use. The items include “I identify with other drug users/drinkers”, “I identify with others in recovery from addiction”, and “I identify with other non-users/non-drinkers”. Responses are on a 5-point Likert scale ranging from 1 - Strongly disagree to 5 – Strongly agree, with higher scores reflecting higher identification with that group.

#### Barriers to connecting

Self-Stigma will be assessed using the Internalized Stigma of Mental Illness Inventory (ISMI-9; [38]). The ISMI-9 contains 9 items. Responses are on a Likert scale ranging from 1 – Strongly disagree to 4 – Strongly agree. The current measure was adapted by the research team in consultation with a consumer advisory group. The term ‘mental illness’ was changed to ‘problematic drug and/or alcohol use’ to adequately reflect stigma specific to the study population. An example item is “I feel out of place because of my problematic drug and/or alcohol use”. Scores from the 9 items are summed together for a total score, and higher scores reflect greater self-stigma.

Fear of Negative Evaluation will be assessed using a brief version of the Social Phobia Inventory, the Mini-SPIN [39]. The Mini-SPIN consists of three items with response options ranging from 0 – Not at all, to 4 – Extremely, which are summed together for a total score. An example of an item is “Do you avoid activities in which you are the center of attention”. Higher scores reflect greater fear of negative evaluation.

To measure theorized barriers to connecting with others (see [10]) subscales of the Young Schema Questionnaire (YSQ-SF; [40]) will be used that relate to: Mistrust, Emotional Inhibition, and Defectiveness/Shame. Each subscale consists of five items, and response options range from 1 – Completely untrue, to 6 – Describes me perfectly. An example of an item from the mistrust subscale includes “I feel that people will take advantage of me”. A total score for each subscale will be computed and higher scores indicate greater theorized barriers to connecting with others.

#### Patient experiences of care

The Patient-Reported Experience Measure for Addiction Treatment (PReMAT) [41] was designed in partnership with people accessing residential AOD treatment services and comprises 33 items that reflect aspects of care most important to people attending these services. An example item is “My day is structured here”. Each item is responded to on a 5-point Likert scale from 1 - strongly disagree to 5 - strongly agree, with total scores ranging from 31 to 155. Higher scores indicate greater levels of positive experience.

To evaluate *participant experience [with Groups for Belonging and TAU]* we will use the Your Experience of Service (YES) Survey [42]. The YES Survey is Australia’s national measure of consumer experience in mental health services. This national questionnaire was developed in partnership with mental health consumers and comprises 26 items designed to gather information from consumers about their experience of care. An example item is “Staff showed respect for how you were feeling”. The 22 items related to ‘experience’ and 4 items related to ‘outcomes’ yield response options ranging from 1 - Never to 5 - Always or 1 - Poor to 5 - Excellent. Scores for two scales (Experience Scale and Outcome Scale) will be summed to provide two summary scores.

### Measures specific to the treatment condition

Group experience will be collected at Week 7 using an 8-item scale developed by our team to examine the experience of completing Groups for Belonging. An example of these items include: “I was able to have a say and share my experiences”. Participants can respond “yes” or “no” to each item.

To evaluate group cohesion over the 6 sessions of *Groups for Belonging*, the Group Climate Questionnaire – Short form (GCQ-S; [43]) will be used at Week 7. The 12 items of the GCQ-S are divided into three subscales measuring *engagement*,* conflict*, and *avoidance*. An example item is “The members liked and cared about each other”. Items across subscales are rated on a 7-point Likert scale from 0 - Not at all, to 6 - Extremely. Scale scores are determined by calculating the average of relevant items.

### Analyses

#### Power analysis

Sample size calculations were performed using the STATA package ‘clustersampsi’ [44]. The control mean loneliness score was assumed to be 49 (*SD* = 10), and intervention mean of 45 (*SD* = 10), based on findings reported across similar samples [45, 46] and indicators of significant and clinically meaningful change across more diverse samples [47]. Intra Cluster Correlation was assumed conservatively to be 0.05. It was calculated that 13 clusters per arm, with 20 participants recruited per cluster, would have 81% power and 5% type 1 error rate to detect a difference in loneliness at 6 months of 4 points. A retention rate of 70% was assumed based on the research team’s track record of achieving excellent follow-up rates across similar samples [48, 49].

#### Data analysis

Statistical analyses will be managed by independent statisticians. Loneliness scores will be analyzed using linear regression in a mixed modelling framework. Fixed effects will include terms for intervention, time point (7 weeks or 6 months), an interaction between intervention and time point, baseline loneliness score, and strata (community-based vs. residential), and random effects for cluster and participant will be included to account for clustering by site, and repeated measurements on participants. The estimated mean difference in loneliness scores between the arms at the primary (6 months) and secondary (7 weeks) time points will be reported, along with 95% confidence intervals, and p-values, as summary measures of the intervention effectiveness.

The analysis set for the primary outcome will be Intention to Treat, however, sensitivity analyses using the Per Protocol analysis set will also be performed. In the case of missing data, multiple imputation methods will be utilized to ensure the analysis set is Intention to Treat. Analysis of secondary outcomes at 7 weeks and 6 months will also utilize linear mixed models (if assumptions of normally distributed residuals and constant variance are met) or generalized linear mixed models otherwise. Fixed effects will include those listed above for the primary outcome variable. Effect estimates for the difference between arms, 95% confidence intervals, and p-values, will be reported for each outcome at each follow-up time point. A sub-group analysis will be performed estimating the difference in change in loneliness from baseline among those participants who reported high loneliness scores at baseline. A secondary sub-group analysis comparing the difference in loneliness scores at 7 weeks and 6 months for residential participants compared to community-based participants will also be performed.

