### Data collection

Demographic characteristics including date of birth, age, postcode, gender, identification as Aboriginal and/or Torres Strait islander, marital status, sexual orientation, dependents/children, living situation, accommodation, education level, employment, job status, history of treatment for AOD use, history of mental and/or physical health conditions, and use of medications will be collected at baseline. All primary and secondary outcomes will be collected at baseline, 7-weeks (i.e., post intervention) and 31-weeks (i.e., 6-months post intervention) and entered directly into Research Electronic Data Capture (REDCap) platform using a laptop (see Table 1). Baseline assessments will be completed either via telephone or, where possible, onsite at the AOD treatment services. Blinded assessment officers will collect the primary and secondary outcome measures via telephone at all timepoints, while research clinicians will collect all other measures at baseline as a means of building rapport with participants. The blinded assessment officers will be trained in the administration of the outcome measures and will receive weekly supervision with one of the senior team members (TD). The assessments will be reviewed weekly for completeness to minimize missing data and improve accuracy. As part of the baseline assessment procedure, contact details for the participant and a nominated alternate contact will be collected to facilitate completion of the follow-up assessment procedures.

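### The secondary-outcome models inherit baseline loneliness as their only stated baseline covariate; no outcome's own baseline is named, which costs precision

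*Protocol article*

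**What the plan says.** The Data analysis section of the protocol article sets out the primary model for loneliness. Its fixed effects are intervention, time point (7 weeks or 6 months), "an interaction between intervention and time point, baseline loneliness score, and strata (community-based vs. residential"); cluster and participant are random effects. On the secondary outcomes it says "Analysis of secondary outcomes at 7 weeks and 6 months will also utilize linear mixed models", with generalized models where the residual assumptions fail. It then fixes the covariates: "Fixed effects will include those listed above for the primary outcome variable". It promises an effect estimate for every outcome at every follow-up.

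The Data collection section states "All primary and secondary outcomes will be collected at baseline, 7-weeks (i.e., post intervention) and 31-weeks". Table 1 marks these as secondary, each with a baseline measurement: "TLFB (i.e. days of use)^2", "Cravings (DAQ-6)^2", "Psychological health (K10)^2", multiple group membership and "Quality of life (AQoL-8D)^2". The first four are repeated at 7 weeks and 6 months. AQoL-8D has entries at baseline and 6 months only, so the Data collection sentence and Table 1 disagree on it.

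**The concern.** In a comparison of follow-up scores, the outcome's own baseline is usually the best single predictor available. Here the covariate list was written for loneliness and then carried over to every other outcome. Read literally, K10 at 6 months is adjusted for baseline UCLA score and not for baseline K10. Because only the two follow-ups are response time points, the outcome's baseline does not enter through the repeated measurements either.

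Two things are at stake, and they are largely the same loss seen from two sides. Intervals for the secondary outcomes are wider than they need be. And a chance difference between arms in, say, baseline K10 is mostly carried into the follow-up estimate. Randomisation of 26 clusters, stratified only by service type, does nothing specific to balance these measures.

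**Working it through.** **The plan's own figure first.** Inputs from the Power analysis section: 13 clusters per arm, 20 recruited per cluster, 70% retention, ICC 0.05, means 49 and 45, SD 10.
- Analysed per cluster: 20 × 0.70 = 14.
- Design effect: 1 + 13 × 0.05 = 1.65.
- Effective n per arm: 13 × 14 / 1.65 = 110.3.
- Noncentral t, 24 df, two-sided 5%: power 81.3%.

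This reproduces the stated 81%. The calculation uses no baseline covariate and concerns loneliness only, so the point raised here does not change it.

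**Reading the covariate list.** The antecedent of the carry-over sentence is the primary model's list. It holds one baseline term, loneliness. No other sentence in the article adds an own-baseline term to the secondary models.

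**Residual variance.** The documents give no correlations, so these are assumptions: r = 0.5 to 0.7 with the outcome's own baseline, and r = 0.2 to 0.4 with baseline loneliness. In a linear model the residual variance is 1 − r² of the unadjusted variance.
- Baseline loneliness: 1 − 0.2² = 0.96 to 1 − 0.4² = 0.84, a reduction of 4% to 16%.
- Own baseline: 1 − 0.5² = 0.75 to 1 − 0.7² = 0.51, a reduction of 25% to 49%.
- Ratio, least favourable pairing: 0.75 / 0.84 = 0.893, or 11% lower.
- Ratio, most favourable pairing: 0.51 / 0.96 = 0.531, or 47% lower.
- Pairing low with low and high with high: 0.75 / 0.96 = 0.781 and 0.51 / 0.84 = 0.607, or 22% and 39% lower.

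If the covariate explains within-site and between-site variance in equal proportion, standard errors scale by √0.893 = 0.945 to √0.531 = 0.729.

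**Power, for illustration.** Same design (14 per cluster, ICC 0.05, 24 df), with an assumed 0.3 SD effect on a secondary outcome:

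| Covariate | Power |
|---|---|
| None | 57% |
| Baseline loneliness (r 0.2 to 0.4) | 59% to 65% |
| Own baseline (r 0.5 to 0.7) | 70% to 85% |

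**Chance imbalance.** Take ICC 0.05 for the secondary outcome as well (an assumption). With 20 per cluster the design effect is 1 + 19 × 0.05 = 1.95, and the SE of a baseline difference between arms is √(2 × 1.95 / 260) = 0.122 SD. With 14 per cluster it is √(2 × 1.65 / 182) = 0.135 SD.

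At r = 0.6 with own baseline and no other adjustment, a one-SE imbalance moves the follow-up difference by 0.6 × 0.122 = 0.073 SD. Baseline loneliness absorbs part of this. Suppose it correlates 0.4 with the outcome's baseline and 0.3 with its follow-up. What remains is (0.6 − 0.3 × 0.4) / √(1 − 0.4²) × 0.122 = 0.524 × 0.122 = 0.064 SD.

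**The case against.** The strongest reply is that the carry-over sentence is not exclusive. It says what the fixed effects will include, and in a condensed article it may be shorthand for the same model structure with each outcome's own baseline. An analysis plan that is not shown may say so. That much stands: a reader might infer that the investigators mean to exclude own baselines, and the text does not prove this. But the article is not silent on covariates. It names the loneliness score specifically, so a plan that uses own baselines would have to read the published sentence as something it does not say.

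A reader might also infer biased secondary results. The documents do not support that. Under randomisation, chance imbalance averages out and is part of the sampling variance that the confidence interval reflects. The analysis as written is valid but less efficient.

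The size is open to challenge too, and the challenge is fair. The 11% to 47% range pairs opposite ends of two assumed ranges. For days of use, the Timeline Follow Back is described as covering the 28 days before treatment entry, and some participants are in residential care, so a correlation of 0.5 or more with later use has no support in the document. It would also be wrong to express the residual imbalance as a share of the 0.4 SD difference in the power calculation, because that difference belongs to loneliness.

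Finally, AQoL-8D does not fit the two-follow-up model at all. The economic analysis plan works with change in quality of life and describes no QALY regression, so nothing there needs amending on this account.

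**Conclusion.** The point holds as a defect of specification in the secondary analyses. As written, baseline loneliness is the only baseline covariate stated for K10, DAQ-6, days of use, multiple group membership and AQoL-8D, while their own baselines are collected and given no stated role in these models. Under the assumed correlations, own-baseline adjustment would lower residual variance by about 11% to 47%, and possibly by less for days of use. These figures are illustrative and apply to linear models. Average validity, the primary analysis and the 81% power are unaffected. It is a should-fix: an improvement in precision at no cost, not a threat to the trial's main conclusion.

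**What to change.** Replace the carry-over sentence with: *Fixed effects will be intervention, time point, their interaction, the baseline value of the outcome being analysed, and strata.* Baseline loneliness may stay as an additional covariate.

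For AQoL-8D, following Table 1, omit the time-point and interaction terms and adjust the 6-month score for its baseline. With one follow-up record per person, the participant random effect also drops out. Bring the Data collection sentence and the promise of estimates at each follow-up into line with Table 1 for this measure.

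The cost is wording only: no new data, visits or participants. Make the change before outcome data by arm are seen, so that the choice of covariates cannot later look data-driven.
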